# RESTART: a stepped-care approach to facilitate return to work for employees with psychological distress: design of a randomized controlled trial

**DOI:** 10.1186/s12889-024-19773-3

**Published:** 2024-08-22

**Keywords:** e-Health, Psychological distress, Participatory approach, Return to work, Stepped-care, Workplace intervention, Mental health

## Abstract

**Background:**

Common mental health problems, such as stress, anxiety and depression, are highly prevalent among workers and often lead to long-term absenteeism and work disability. Effective elements found in previous researched interventions were to explicitly focus on return to work (RTW) and not solely on symptom reduction, to take into account the employees’ cognition towards RTW and to include the workplace environment. Based on these elements, a stepped-care approach was developed. The aim of this paper is to present the study design of a randomized controlled trial (RESTART), evaluating the effectiveness of the stepped-care approach on lasting RTW and the implementation process.

**Methods:**

RESTART is a randomized controlled trial with a 2 × 2 factorial design and a follow-up of one year. Employees eligible for this study are those who reported sick within 2 to 8 weeks with psychological distress based on a distress screener. Participants will be randomized to a group receiving a tailored e-Health app or usual care, as well as randomized to a group receiving a Participatory Approach (PA; conversational method) in the workplace or usual care. The PA will however only be provided in case of persistent sickness absence at 8 weeks. Measurements take place at baseline, after the e-Health intervention period (3 months), and after the PA intervention period (6 months) and 12 months. Primary outcome is lasting RTW, defined as full RTW in previous or equal work for at least four consecutive weeks. Secondary outcomes are (the severity of) stress-related symptoms, total number of sickness absence days, self-efficacy for RTW and self-reported health. A process evaluation including a realist evaluation will also be conducted.

**Discussion:**

Early intervention that focuses on RTW, the cognition towards RTW despite symptoms and involves the workplace environment, plays a crucial role in managing sickness absence among employees with psychological distress. If effective, the stepped-care approach is relevant for employees, employers and society as a whole.

**Trial Registration:**

ISRCTN: 90663076. Registered on 5 October 2023.

**Supplementary Information:**

The online version contains supplementary material available at 10.1186/s12889-024-19773-3.

## Background

Common mental health problems, such as depressed mood, anxiety and stress, are of growing concern in today’s workforce. Common mental health problems affect the well-being, productivity and economic prosperity of individuals, organizations and society as a whole [1]. In 2019, 42% of sickness absence days in the Netherlands were caused by common mental health problems [2]. As work provides structure in one’s day, social contacts and contributes to a feeling of appreciation, not being able to work due to common mental health problems has a huge impact on the employee, together with being at high risk for long-term absenteeism [3, 4]. The employer and society are confronted with high costs due to absenteeism and incapacity to work caused by common mental health problems. Recently, a Dutch study showed that on average, one episode of sickness absence due to stress-related health problems lasted 101 working days, which led to costs for the employer of above 19 thousand euros [3]. It is also known that the probability of eventual return to work (RTW) declines with longer absence [5], which poses a challenge for absenteeism due to common mental health problems because of its long-term nature.

When employees on sickness absence with common mental health problems currently receive treatment, these treatments mainly focus on reducing symptoms [6]. However, research has shown that a decrease of symptoms does not imply an immediate (partial) RTW [6–8]. Consequently, there has been a growing recognition of the importance of promoting RTW as a key goal of treatment and involve the workplace environment in the rehabilitation of employees with common mental health problems [9–12]. This is also driven by the emerging importance of offering interventions that provide the greatest patient value [13] and being able to work is considered one of those values [8, 14].

Some previously evaluated interventions that aimed to facilitate RTW for employees with common mental health problems showed mixed results. An e-Health program to facilitate RTW based on psychological principles, such as psycho-education, cognitive behavioral therapy (CBT) and problem-solving therapy (PST) was effective on duration to first RTW (50 days) compared to conventional sickness guidance (usual care; 77 days). The e-Health program was not effective on lasting RTW [11]. A process evaluation of the e-Health program revealed that adherence of employees to the program varied between 13 and 90% [15], which might have impacted the full realization of the programs potential.

Another study evaluated the effectiveness of a Participatory Approach (PA) for employees on sickness absence with common mental disorders [12]. The PA is a stepwise process between the employee and his or her supervisor with the aim to reach consensus about obstacles and solutions to enable RTW, under guidance of a RTW-coordinator. Overall, the PA had no effect on lasting RTW, except for the subgroup of employees who indicated at baseline that they were open to RTW despite symptoms. For these employees, with a positive cognition towards RTW despite symptoms, the PA significantly reduced the time to lasting RTW (55 days) compared to conventional sickness guidance (usual care; 120 days) [12].

As the e-Health program was effective on first RTW – but not lasting RTW, and the PA was effective only for the subgroup who had a positive cognition towards RTW despite symptoms, we propose a stepped-care approach to combine these effective elements. The stepped-care approach starts with a low-intensive e-Health early in the absenteeism process. The e-Health consists of a tailored program which focuses on developing and reinforcing a positive cognition towards RTW. If RTW is not reached, the e-Health program is followed by a more intensive PA that has greater involvement of the workplace environment. The combination of these elements in a stepped-care approach aiming to facilitate a timely and lasting RTW is considered potentially effective. The aim of this paper is to describe the design of the RESTART (*R*eturn to work for *E*mployees with distress: a *ST*epped c*AR*e *T*reatment) study, which includes an evaluation of the effectiveness of the stepped-care intervention on lasting RTW by a randomized controlled trial and a process evaluation.

## Methods

### Design and setting

The study is a randomized controlled trial (RCT) with a 2 × 2 factorial design. This design allows to test the main effects of the e-Health and PA separately, as well as their combined effect on lasting RTW. The study includes a baseline assessment and 3 follow-up assessments at 3 months (after e-Health), 6 months (after PA) and 12 months. Afterwards a process evaluation will be conducted following the Steckler and Linnan framework [16, 17], including a realist evaluation [18]. The process evaluation aims to provide insights in what elements of the stepped-care approach work, for whom and under which circumstances and to evaluate to what degree the implementation of the stepped-care approach was conducted as intended.

The study will be carried out in a large Dutch occupational health service (OHS) organization. The OHS consists of about 4,000 employees – mainly white-collar workers. Occupational health (OH) practitioners from the OHS organization, which has multiple branches spread over the Netherlands, are involved in this study. The core business of the OHS is to offer services to different organizations with the goal to increase the health of workers, promote sustainable employability, prevent sick leave, and offer support for RTW after sickness absence. The task of the OP in the Netherlands is to prevent work-related diseases and to support workability and RTW after sickness absence. The OH practitioner collaborates with the OP and works in task delegation of the OP to reduce the work pressure of the OP. Both OPs and OH practitioners have consultations with employees to promote workplace health, to prevent sickness absence, or to support RTW. Participants will be recruited within the OHS organization itself and their partners.

The trial has been approved by the Medical Ethics Committee of the Amsterdam Academic Medical Center (2023.0474) and is registered in the ISRCTN registry (ISRCTN90663076). Signed informed consents will be obtained from each participant.

### Study population

Participants will be employees of the OHS network, who reported sick for a minimum of 2 weeks and a maximum of 8 weeks. Participants are eligible if they (1) filled in the distress screener based on the Four-Dimensional Symptoms Questionnaire (4DSQ), (2) met the distress criteria and (3) signed informed consent.

Exclusion criteria will be (1) severe psychiatric disorders (suicidal risk, schizophrenia, bipolar disorder), (2) treatment for terminal or chronic illnesses that preclude their ability to resume work in the near future (e.g. chemotherapy or cardiac surgery), (3) a labour dispute between the employee and the employer, involving legal action, (4) working less than 12 h per week according to contract, (5) pregnancy, (6) no proficiency of the Dutch language and (7) no access to the internet.

Within the literature, different terminology and definitions are used for describing (different subgroups of) mental health problems. For example, common mental disorders, mental health problems, psychological complaints and distress are used. In the current study we will refer to employees with psychological distress. Psychological distress is defined as self-reported complaints of non-specific stress symptoms, depressed mood, anxiety and/or somatization.

### Recruitment and procedures

Recruitment will start in April 2024, and will be ongoing until the necessary number of participants is reached. Within one week of absenteeism, the employee will be notified of the study by means of a digital information letter that is automatically sent to the employee via the absence registration process of the OH physician. The digital information letter will contain all required information about the study and a QR-code (and website link) that will lead to a safe online questionnaire that contains the distress screener and questions regarding the exclusion criteria. The distress screener, derived from the 4DSQ [19], consists of three questions and is a valid instrument for identification of distress in employees on sickness absence [20]. If the employee is eligible and willing to participate, they will receive the informed consent form digitally from the researchers, together with the possibility to schedule a (video)call with the researcher or the OH practitioners in case they require more information before they want to participate, i.e. sign informed consent. After online informed consent is obtained, the participant is invited to the online baseline assessment.

### Randomization and blinding

Randomization takes place on employee level. In addition to usual care, participants can receive e-Health and/or PA. This leads to a 2 × 2 factorial design, which allows to test the main effects of e-Health and PA separately, as well as the combined effect on lasting RTW. Therefore, participants are randomized twice, which results in two comparisons in the main outcome analysis: PA vs. not PA and e-Health vs. no e-Health. On top of usual care participants receive either: (1) e-Health and PA, (2) e-Health only, or (3) PA only (see Fig. 1). A time schedule of enrolment, interventions, and assessments are presented in Fig. 2. Both randomizations take place directly after baseline to ensure even-sized groups. If, however, participants who are assigned to receiving PA (partially) returned to work before PA starts, they will not receive PA.

A computer-based randomization list, generated by an independent researcher, will be used to allocate participants, based on their participant-ID, to one of the four groups. Before the statistical analyses are performed the condition-IDs are recoded by an independent researcher, which allows the primary researcher to be blinded for the allocation and the RCT to be single-blind.

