### Sample size

The sample size was calculated based on number of cases needed to identify an effect on time to (lasting) RTW. Based on previous research of RTW interventions for employees with psychological distress a hazard ratio (HR) was chosen of 1.8 [11, 12, 21]. A sample size calculation was performed with an HR of 1.8, alpha of 0.5 and power of 80%, which generated a total sample size of 144 participants, 36 participants per group. Accounting for a loss-to-follow up of 15% after 12 months, we aim to include 166 participants.

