#### Participatory approach (PA)

The Participatory approach (PA) is coordinated by one of the independent RTW-coordinators. Participants will receive PA six weeks after baseline; after completing the e-Health program or after care-as-usual, depending on their respective condition. The RTW-coordinator plans three meetings: the first meeting with the employee, the second meeting with his or her supervisor and the third meeting with the employee and supervisor. These meetings are scheduled shortly after each other (e.g. within two weeks).

In the first meeting, the employee is guided by the RTW-coordinator to perform a task-analysis and obstacle inventory. In a guided conversation, the employee first lists their main responsibilities and activities in their work, and uses this list to identify obstacles for RTW. The first meeting finishes after ranking the obstacles for RTW based on priority, frequency and perceived severity. If the employee received e-Health they already practiced with this and they can use that list to refine obstacles together with the RTW-coordinator. At the second meeting, the task-analysis and obstacle inventory are performed from the perspective of the supervisor, together with the RTW-coordinator. In the third meeting, the employee and his or her supervisor discuss the identified obstacles and brainstorm about solutions for these obstacles. Under guidance of the RTW-coordinator, they will rank the solutions, based on feasibility, solving capability and short-term applicability. The third meeting concludes with a RTW plan. This RTW plan includes the chosen solutions based on consensus between the employee and the supervisor, and is formulated in terms of who is responsible, to do what and when. At the end of the meeting, the RTW-coordinator plans an evaluation moment with the employee and the supervisor. The chosen solutions are to be implemented in the weeks after the third meeting, ideally within a time frame of 3 months. After three months the actual implementation of the solutions will be evaluated by the RTW-coordinator, together with the employee and the supervisor.

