#### Data analysis

Descriptive statistics will be provided for all relevant variables at baseline. To investigate the effectiveness of the interventions of the stepped care approach on lasting RTW a cox-regression will be conducted. To determine the effect of e-Health separately, the group who received [e-Health and PA] will be combined with the [e-Health only] group, and compared to the control- and [PA only] group. The same logic applies to PA; the PA groups will be combined and compared to the control- and [e-Health only] group. To test whether the combination of e-Health and PA in a stepped-care approach is superior to the separate interventions alone, we will study the interaction between PA and e-Health. For the secondary outcomes, depending on the type of outcome measure (continuous/categorical) generalized linear models or mixed effects logistic regression will be used. Analyses are conducted both unadjusted and adjusted for potential confounders. Additionally, effect modification of several factors, such as the (severity of) stress-related symptoms and cognition towards RTW despite symptoms, will be investigated by using interaction terms.

All analyses will be performed according to the intention-to-treat principle (ITT), which implies that all employees are analyzed according to the group they were assigned to, regardless of whether they actually received the intervention.

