### Strengths and limitation

The 2 × 2 factorial design allows to test the main effects of the e-Health and PA separately, and the combined effect on lasting RTW, while keeping the sample size relatively small. A possible limitation of the 2 × 2 factorial design is that it requires both randomizations directly after baseline, but it is unknown how many employees eventually will complete PA, as this depends on persistent sickness absence of at least 6 weeks after baseline.

Another potential limitation of the current study could be non-adherence to the e-Health program. The e-Health program is mainly completed independently by the employee, and therefore relies more heavily on individual motivation. To minimize the chance of non-adherence employees will be stimulated to engage with the program [23] and are offered the possibility to have a 30 min consult with the OH practitioner. Furthermore, the patterns of app usage and adherence to the program will be investigated by means of the process evaluation.

The realist evaluation and the process evaluation will provide a deeper understanding of what elements are a success or failure, and why. This will provide important knowledge for further development and implementation of the stepped-care approach in practice.

The results from the effect- and process evaluations, together with perspectives from all stakeholders (employees, employers and OH practitioners), will provide a broad insight in the effectiveness of the stepped-care approach and its elements on lasting RTW for employees on sickness absence with psychological distress. These insights can be of large potential value to employees, employers and occupational practice.

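### The 80% power at HR 1.8 is not supported for the PA comparison: PA starts six weeks after baseline and is withheld from early returners, yet it is tested as one hazard ratio over everyone randomised

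*Protocol article*

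**What the plan says.** All of the following is in the protocol article.

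- **Randomization and blinding:** both allocations are made directly after baseline, and PA against no PA is one of two comparisons in the main outcome analysis. If "participants who are assigned to receiving PA (partially) returned to work before PA starts, they will not receive PA".
- **Participatory approach (PA):** "Participants will receive PA six weeks after baseline". The Abstract instead ties PA to absence persisting at 8 weeks.
- **Data analysis:** Cox regression compares the two PA groups combined with the two non-PA groups combined. Everyone is analysed as assigned, "regardless of whether they actually received the intervention".
- **Sample size:** "a hazard ratio (HR) was chosen of 1.8" from earlier return-to-work (RTW) research, with "alpha of 0.5 and power of 80" percent. This gives 144 participants (36 per group), raised to 166 for 15% loss. The 1.8 is not split by intervention, and no event proportion is given.
- **Strengths and limitation:** a limitation of the design is that "it requires both randomizations directly after baseline, but it is unknown how many employees eventually will complete PA". This is not carried through to power.
- **Background:** for the earlier PA trial, "Overall, the PA had no effect on lasting RTW, except for the subgroup of employees" with a positive cognition towards RTW.

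**The concern.** For the first six weeks the PA and no-PA margins receive the same care. Provided participants do not react to knowing their PA allocation, the hazard ratio in that period is 1. Participants who have returned only partially by week 6 can still reach the primary outcome later, but without ever receiving PA. A single Cox HR over all randomised participants averages these untreated events with the treated ones, so it lies closer to 1 than the effect PA has on those who get it.

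The sample size makes no allowance for this. If 1.8 describes recipients, a PA that works as assumed has a materially larger chance of being missed than the 20% the article implies. A null result could then be read as evidence against PA when the comparison was short of power.

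**Working it through.** **Inputs from the article.** HR 1.8; power 80%; 144 analysed and 166 enrolled; 15% loss; PA from day 42 after baseline; 12 months of follow-up; equal PA and no-PA margins.

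**Assumptions.** The printed alpha of 0.5 is read as 0.05, two-sided. Hazards are constant, apart from the PA effect. Usual-care median time to lasting RTW is 90 to 300 days from baseline. The article's only such figure is 120 days, in a subgroup of the earlier PA trial. E-Health has no effect unless stated.

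**1. The article's own figure.** Events needed (Schoenfeld) = (1.96 + 0.842)² / (0.25 × (ln 1.8)²) = 7.85 / (0.25 × 0.3455) = 91. Freedman's formula gives 97. Neither is 144. The two agree only if 91/144 = 63% to 97/144 = 67% of participants have the event, which is not stated. The 166 is 144 × 1.15 = 165.6, and 166 × 0.85 leaves 141.

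**2. Dilution at 91 events.** If a share f of events carries no PA effect, the average log HR is about (1 − f) × ln 1.8, and power is Φ(√91/2 × (1 − f) × 0.588 − 1.96).

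| f | Power |
|---|---|
| 0 | 80% |
| 10% | 71% |
| 20% | 61% |
| 30% | 50% |

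**3. Delay only, 166 enrolled with 15% loss.** This log-rank simulation sets HR to 1 before day 42 and 1.8 afterwards in the PA margin. Only full return blocks PA.

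| Usual-care median (days) | Events | Share before day 42 | Average HR | Power |
|---|---|---|---|---|
| 120 | 146 | 24% | 1.58 | 75% |
| 150 | 138 | 21% | 1.61 | 77% |
| 200 | 125 | 18% | 1.64 | 77% |
| 260 | 112 | 16% | 1.65 | 74% |
| 330 | 98 | 14% | 1.66 | 69% |

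- Hand check of the first row: 0.76 × 0.588 = 0.447, an HR of 1.56. With 146 events, Φ(6.04 × 0.447 − 1.96) = Φ(0.74) = 77%.
- Over medians of 90 to 300 days the result is about 72-76%. A repeat at 90, 120, 180, 240 and 300 days gave 70-78%, so single cells move by about two points.
- With no delay the same model gives 94%, 91% and 88% at medians of 150, 200 and 260 days. The shortfall therefore comes from the delay, not from the number enrolled.
- If e-Health works, more people return before PA starts. With an e-Health HR of 1.8 and a 120-day median, PA power is 66%.
- If PA starts 56 days after baseline, power at a 120-day median is 67%.

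**4. Adding the partial-return rule.** The article gives no proportion of early partial returners, so this step is a range.

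- With an assumed 20% who return partially before week 6, unrelated to later lasting RTW, power is about 48-55%.
- At a 120-day median, f is roughly 24% + 20% × 76% = 39%. The formula in step 2 with 146 events then gives an HR of 1.43 and 58%, slightly above the simulated range.
- The unrelatedness assumption matters most. Take a median of 77 days to first RTW (the Background's usual-care figure from the earlier e-Health trial) and 120 days to lasting RTW. Power is 74% if early partial returners are the faster returners, and 39% if early partial return is independent of lasting RTW.

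**5. Starting the clock at week 6.** An analysis of those still fully absent at day 42, excluding the assumed 20% of partial returners from both margins, has about 68-79% power with 166 enrolled.

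**The case against.** **The 1.8 may already be an intention-to-treat average.** If so, the 80% stands as far as this point goes. The article does not say, and the sources for 1.8 are not shown. With 24% of events unaffected, an average of 1.8 needs an HR in recipients of exp(0.588/0.76), about 2.2. The Background's subgroup result, 55 against 120 days, has a ratio of 2.2 and would match that if the figures are medians under constant hazards. It belongs to a subgroup, however, and the same trial found no overall PA effect on lasting RTW. The objection makes the conclusion conditional; it does not remove the need to say what 1.8 is.

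**There may be slack.** If nearly all 144 have the event, and no more than about 20% of events carry no PA effect, power is Φ(6 × 0.8 × 0.588 − 1.96) = 81%. This stands as a possibility, but the article gives no event proportion to support it.

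**The issue is disclosed.** Only uncertain completion of PA is disclosed. The power claim is left unchanged.

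**Withholding PA from returners is the strategy under test.** This stands. A reader might infer that the intention-to-treat Cox analysis is wrong and that an analysis from week 6 should replace it. The documents do not support that. Step two is meant only for persistent absence, and the all-randomised comparison is a valid test of that policy. The week-6 analysis answers a different question, in a subset that e-Health may have shaped. It is protected by randomisation only if PA allocation was undisclosed until then. The article places both allocations at baseline and describes blinding of the primary researcher only.

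**Conclusion.** The point holds as a mismatch between the power statement and the effect that the planned analysis estimates. For PA, 80% power at HR 1.8 is unsupported as written. If 1.8 is the effect in recipients, power with 166 enrolled is about 72-76% when only full return blocks PA, and about 48-55% with an assumed 20% of unrelated partial returners. The direction follows from the article's own rules. The size rests on assumed return rates, an unstated event proportion and the unknown link between early partial return and lasting RTW.

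Two stronger readings go too far. One is that power is lower still because 15% loss is applied to 144; the article enrols 166 to absorb that loss. The other is that starting the clock at week 6 restores 80%; once partial returners are excluded it gives about 68-79%.

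E-Health starts after baseline, so this rule does not reduce its power.

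**What to change.** 1. State whether 1.8 is the intention-to-treat average or the effect in recipients after PA starts.
2. Restate PA power for the all-randomised analysis as a range, based on 166 enrolled, with the assumed return rates, event proportion and share of partial returners written out. Limit the 80% claim to e-Health.
3. Keep the intention-to-treat Cox comparison as primary.
4. Prespecify a supportive Cox analysis of participants still fully absent at the planned PA start. Use the same absence rule in the PA and no-PA arms, start the clock at that point and include e-Health in the model. Interpret it as a randomised comparison only if PA allocation was undisclosed until then, and record whether it was.
5. Reconcile the six-week statement in the PA section with the eight-week statement in the Abstract, including the day from which each is counted, because the date in item 4 depends on it.

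The cost is protocol and analysis-plan wording, plus an absence status at PA start for all arms, taken from the diaries or occupational health service records already planned. The downsides are that the stated PA power will be lower and that the supportive estimate applies only to employees still absent at that point.
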